# Community intervention for child tuberculosis active contact investigation and management: study protocol for a parallel cluster randomized controlled trial

**DOI:** 10.1186/s13063-021-05124-9

**Published:** 2021-03-02

**Keywords:** Contact tracing, Preventive therapy, Pediatric tuberculosis, Community intervention, Tuberculosis symptom screening, Cluster randomized controlled trial

## Abstract

**Background:**

There are major gaps in the management of pediatric tuberculosis (TB) contact investigation for rapid identification of active tuberculosis and initiation of preventive therapy. This study aims to evaluate the impact of a community-based intervention as compared to facility-based model for the management of children in contact with bacteriologically confirmed pulmonary TB adults in low-resource high-burden settings.

**Methods/design:**

This multicenter parallel open-label cluster randomized controlled trial is composed of three phases: I, baseline phase in which retrospective data are collected, quality of data recording in facility registers is checked, and expected acceptability and feasibility of the intervention is assessed; II, intervention phase with enrolment of index cases and contact cases in either facility- or community-based models; and III, explanatory phase including endpoint data analysis, cost-effectiveness analysis, and post-intervention acceptability assessment by healthcare providers and beneficiaries. The study uses both quantitative and qualitative analysis methods. The community-based intervention includes identification and screening of all household contacts, referral of contacts with TB-suggestive symptoms to the facility for investigation, and household initiation of preventive therapy with follow-up of eligible child contacts by community healthcare workers, i.e., all young (< 5 years) child contacts or older (5–14 years) child contacts living with HIV, and with no evidence of TB disease. Twenty clusters representing TB diagnostic and treatment facilities with their catchment areas are randomized in a 1:1 ratio to either the community-based intervention arm or the facility-based standard of care arm in Cameroon and Uganda. Randomization was stratified by country and constrained on the number of index cases per cluster. The primary endpoint is the proportion of eligible child contacts who initiate and complete the preventive therapy. The sample size is of 1500 child contacts to identify a 10% difference between the arms with the assumption that 60% of children will complete the preventive therapy in the standard of care arm.

**Discussion:**

This study will provide evidence of the impact of a community-based intervention on household child contact screening and management of TB preventive therapy in order to improve care and prevention of childhood TB in low-resource high-burden settings.

**Trial registration:**

ClinicalTrials.gov NCT03832023. Registered on 6 February 2019

**Supplementary Information:**

The online version contains supplementary material available at 10.1186/s13063-021-05124-9.

## Background

Tuberculosis (TB) is an infectious disease causing incident cases of disease in around 10 million people worldwide in 2018 [1]. The World Health Organization (WHO) estimated that 11% of the TB cases in 2018 were in children (< 15 years). However, a modeling study has estimated that the pediatric caseload in high-burden countries is as high as 15–20% of all TB cases [2]. The mortality rate in undetected untreated children is estimated to be 21.9% for children of all ages and rises to 43.6% in young children of less than 5 years [3]. Improving case detection and treatment of this high-risk group of young children is particularly challenging due to diagnostic limitations and clinical overlap with other common severe diseases of infants and young children in resource-limited settings.

Research has consistently shown that TB disease in young children usually occurs soon after exposure and infection, that the risk of disease if infected is high, and that TB preventive therapy (TPT) can significantly reduce the risk of disease following exposure and infection [4]. A meta-analysis reported that 10% of young child contacts had TB disease at the time of screening, and 35% had evidence of infection [5]. A recent individualized participant meta-analysis found that the effectiveness of tuberculosis preventive treatment (TPT) was 63% (95% CI 53–70%) among all exposed children and 85% (95% CI 80–89%) among those with evidence of infection [4]. Therefore, the rapid identification and management of exposed children in the households of TB disease cases is a critical opportunity to detect, treat, and prevent TB. Although recommended for decades, household child contact screening and TPT have been poorly implemented in high-burden and resource-limited countries. For many years, children were considered lower priority due to being less infectious and therefore contributing less to TB transmission than adults [6].

The WHO End TB Strategy and ambitious targets for coverage of screening and TPT in the Global Plan to End TB demonstrate political will and provide renewed opportunity to close the wide policy-practice gap [7, 8]. The policy-practice gaps observed in the screening and management of child contacts are driven by health system and human resource challenges as well as the many challenges faced by families in bringing their children to the health facility [9–13]. In most low-resource countries, the index case is asked to bring all child contacts to the health facility for TB screening, and yet many barriers arise when applying this recommendation such as scheduling or financial challenges, transport costs, long waiting periods in settings with risks of further exposure, and families or even healthcare workers’ reluctance to apply these guidelines as they do not always understand the rationale, potential benefits, or risks when the child is well [13–17]. Community-based household contact screening of children in the household is likely to improve TB disease case detection [8, 18–20].

The use of classical tuberculin skin test (TST) to identify child contact with TB infection who will benefit from the TPT and the need of chest radiography (CXR) in addition to symptom screening to exclude TB disease before initiation of TPT have both operational challenge that contributes to the lost proportion of child contacts initiated on TPT for a long time [13]. However, there is evidence that the additional yield of TB disease detection from CXR in asymptomatic child contacts is extremely low [9, 21–23]. In addition, WHO has recommended since 2006 that high-risk child TB contacts—young (< 5 years) or are living with human immunodeficiency virus (HIV) of any age—receive TPT after exclusion of TB disease without systematically confirming TB infection with TST [24, 25]. Therefore, a symptom-based approach that does not require further investigations for asymptomatic child contacts could facilitate a more decentralized, community-based implementation to initiate TPT in asymptomatic children [8]. In addition, the recent WHO recommendations [6] that include shorter TPT combination regimens (isoniazid and rifampicin or rifapentine for 3 months) are associated with improved adherence compared to the standard TPT regimen of isoniazid monotherapy for at least 6 months and provide an important opportunity for increasing completion of TPT [9, 26, 27]. Further, follow-up of children receiving TPT at the household could further improve TPT completion rates and could be easily integrated with activities to support treatment of TB disease of the index cases in the household.

There is no published study that has evaluated the impact on the cascade of care of pediatric TB case detection and preventive therapy management of a community-based approach compared to a facility-based standard of care. We therefore aim to evaluate the implementation of a community-based approach to child TB contact screening and management in two TB-endemic African countries.

## Methods

### Study objective and endpoints

The primary objective of this study is to compare the proportion of household child TB contacts eligible for TPT who initiate and complete TPT under a facility-based standard of care and under a decentralized community-based intervention model of care for contact screening and management.

The corresponding primary endpoint is the proportion of child TB contacts < 5 years of age and HIV-infected children of 5–14 years of age who are declared by the index case and who initiate and complete the TPT.

The secondary objectives compare the aforementioned models in terms of (i) cascade of care of TPT initiation and completion in child contacts < 5 years or HIV-positive children 5–14 years; (ii) cascade of care for TB detection and treatment in all included contacts; (iii) tolerability and adherence in children initiated on TPT; (iv) acceptability and feasibility of the two models by the parents/guardians, health personnel, and community; (v) the effect of the community-based intervention on the number of adult contacts diagnosed with TB; and the cost-effectiveness. The number of children and adults diagnosed with TB and the number of children initiated on TPT will be also compared before and after the intervention.

The secondary endpoints of the study are presented in Table 1.

**Table 1 Tab1:** Secondary endpoints of the CONTACT study

General secondary endpoints	Detailed secondary endpoints
Cascade of care for the initiation and completion of TPT of child contacts < 5 years or HIV-infected 5–14 years and reasons of dropouts at different steps of the cascade	Number of screened children and proportion of children screened among child contacts < 5 years or HIV-infected 5–14 years declared by the index case
	Proportion of children potentially eligible for TPT: TB disease excluded
	Proportion of children eligible for TPT after exclusion of contraindication to TPT
	Proportion of children started on TPT among those eligible for TPT
	Proportion of children who did not complete TPT among those started on TPT and reasons of interruptions
Cascade of care for TB detection of child contacts	Proportion of children with symptoms suggestive of TB: presumptive TB
	Proportion of presumptive TB cases investigated for TB
	Proportion of children diagnosed with TB
	Proportion of children with TB diagnosis who are started on TB treatment
Cascade of care for TB detection of adult contacts	Number of adults screened and proportion of adults screened among household identified adult contacts
	Proportion of adults with symptoms suggestive of TB: presumptive TB cases
	Proportion of adults presumptive TB cases diagnosed with TB
Safety and treatment adherence for children under TPT	Proportion of children with serious adverse events
	Proportion of children with adverse events of interest: peripheral neuropathy, clinical hepatotoxicity
	Ratio of dose taken as indicated (ticked) on the treatment card by the parent/guardian over the total number of doses to be taken by prescription
Endpoints at 6 months	Treatment outcomes of children started on TB treatment
	Proportion of children diagnosed with TB after initiation of TPT: during and after TPT
	Proportion of children diagnosed with TB among those who were not started on TPT and were not diagnosed with TB at baseline assessment
Before-after comparison for TB adult and pediatric cases and for TPT initiation and completion from health facility registers	Number of patients diagnosed with TB and registered
	Proportion of children among all patients diagnosed with TB and registered
	TB treatment outcomes of patients (adults and children) diagnosed with TB and registered
	Number of children started on TPT
	Completion rate of children started on TPT
Acceptability and feasibility of the intervention	Attitudes, willingness, and motivation to have a visit in their household
	Myths, anticipated fears, stigma, and risks of having a visit in their household
	Actual experiences with household visits
	Perception of the disease, its risk, and the notion of prevention, including TPT
	Description of critical events during house visits and how these were dealt with
	Identification of main constraints
Fidelity of the study	Proportion of delivered activities compared to the intended activities of the model
Cost-effectiveness of the intervention	Costs of CHW/community nurse assessment and treatment
	Costs of facility-based assessment and treatment
	Other facility costs (overheads, diagnosis, hospitalizations)
	Direct parent/guardian costs (related to care)
	Indirect parent/guardian costs (unrelated to care, e.g., dissaving, travel costs)

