### Description of the intervention

#### Facility-based model

This model implements a “passive” approach to the screening and management of household contacts (see definition in the “Study population” section) at the facility level as per current practice. Implementation follows current National Tuberculosis Program (NTP) recommendations, except that a 3-month regimen of daily rifampicin-isoniazid (3RH) as a fixed-dose combination (FDC) is offered as TPT to eligible child contacts. In the context of the study, sites also benefit from additional data collection and trainings with follow-up support for the facility staff.

When a person is diagnosed with bacteriologically confirmed pulmonary TB (index case), the facility staff in charge of TB (TB focal person) asks the index case to bring all household contacts with TB-related symptoms, all young (< 5 years) child contacts or older (5–14 years) child contacts living with HIV or exposed to HIV, irrespective of symptoms, to the health facility for evaluation for TB disease or for eligibility for TPT. This facility-based model is currently implemented in district hospitals in Cameroon for child contacts under 5 years old, but poorly applied for child contacts 5–14 living with HIV. In Uganda, the NTP allows household contact tracing when feasible but evaluation, TPT initiation, and follow-up are required to be done at the facility. In practice, due to lack of transport, the household contact tracing was poorly implemented. In both countries, at facility, TB investigations include clinical examination, sample collection for smear microscopy or Xpert MTB/RIF testing, and CXR when available and indicated, i.e., Xpert is negative or not done. Any contact diagnosed with TB is commenced on TB treatment, registered, and provided with treatment support and follow-up as per NTP guidelines. All sites are supported by the CaP TB program reducing the risk of heterogeneity of diagnosis and treatment of pediatric TB between sites and the two countries. Asymptomatic children who are eligible to receive TPT as 3RH (or 6H if drug-drug interactions with antiretroviral therapy preclude the use of rifampicin) are initiated at the facility with monthly follow-up (Fig. 1). The schedule of the facility-based model is presented in Table 2.

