### Statistical analysis

#### Primary analysis

The denominator for the analysis of the primary endpoint is the number of child contacts < 5 years and HIV-infected 5–14 years declared by the index case at the facility during the inclusion visit. Since discrepancies can be expected between what is declared by the index case and what is observed during contact screening, a sensitivity analysis will be performed using as denominator the number of children < 5 years of age and HIV-infected children of 5–14 years of age identified during the screening. An additional sensitivity analysis will be performed including only participants that followed all study procedures (per-protocol approach) among the declared and then enrolled child contacts. Dropping out of the cascade of cares and potentially being lost to follow-up can be the consequence of the models of care under evaluation. Therefore, lost to follow-up will be kept in the primary outcome analysis. They will be removed from the sensitivity per-protocol analysis.

A generalized linear mixed model with a binomial distribution and logit link function will be used to perform individual-level analysis adjusting for clustering. The regression model will include the fixed effect of treatment assignation and country and one random-effect for the cluster. A degree-of-freedom correction will be applied (between-within method) to deal with the type I error inflation due to the small number of clusters. The primary analysis will focus on the difference between the two study arms adjusted for country, and a secondary analysis will add an adjustment for unbalanced factors (urban/rural, district size) identified in the baseline assessment. For the analysis of the secondary outcomes, a similar mixed model will be used with the same random effects and correction method, focusing on each endpoint of the cascade of care for initiation and completion of TPT and each endpoint of the cascade of care for TB detection. The same model will be applied for the sensitivity analyses.

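### Two secondary TPT-cascade endpoints are compared between arms within groups formed after allocation, and no listed endpoint gives initiation alone among declared children

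*Protocol article*

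**What the plan says.** The protocol article (Study objective and endpoints) makes the cascade a between-arm question: "The secondary objectives compare the aforementioned models in terms of (i) cascade of care of TPT initiation and completion". Two Table 1 rows state a conditional denominator: "Proportion of children started on TPT among those eligible for TPT" and "Proportion of children who did not complete TPT among those started on TPT and reasons of interruptions". The first row of the same block, children screened, keeps declared children as its denominator. The two eligibility rows between print none.

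Under Primary analysis, the primary denominator is the children in the target groups "declared by the index case at the facility during the inclusion visit". On the model, the text says "The regression model will include the fixed effect of treatment assignation and country", with a random effect for cluster. Secondary outcomes get a similar model, "focusing on each endpoint of the cascade of care for initiation and completion of TPT". The same section explains why losses stay in the primary analysis: "Dropping out of the cascade of cares and potentially being lost to follow-up can be the consequence of the models of care under evaluation".

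The route into the cascade differs by arm. Under Facility-based model, the TB focal person "asks the index case to bring all household contacts with TB-related symptoms", together with children under 5 and older children living with or exposed to HIV, whatever their symptoms. Under Community-based model, an index case who agrees receives a team at home, and eligible children without symptoms get a further home visit to start TPT.

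**The concern.** Randomisation of clusters makes the arms comparable for all children entering the study. It does not make them comparable for the children who reach a later step when the model of care itself decides who gets there. A facility-arm child becomes a starter only if the family makes the trip. A community-arm child can become one without it. The Background names transport, cost, waiting and reluctance as barriers to bringing children in. Facility-arm follow-up is also monthly at the facility, so the same traits plausibly affect completion. If the home model reaches families who would not have attended, its starters include children who are harder to retain.

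The contrast among starters is the natural place to look for an effect of home follow-up on completion, which the Background puts forward as a benefit of the approach. A biased contrast there could understate or hide that benefit. Initiation has a related gap. It is listed among eligible children, a group that also forms after allocation, and no row gives it among declared children.

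**Working it through.** **Is an arm test planned in these groups?** The secondary objective compares the models on the cascade. The model for cascade endpoints is similar to the primary model, which contains arm. The denominators are eligible and started children. So an arm effect within post-allocation groups is prespecified, not left open.

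**Planning figure.** The point does not depend on the sample-size calculation, but the same design-effect formula is used below. With 1500 children in 20 clusters (mean m = 75), ICC 0.01 and cluster-size CV 0.50:

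DE = 1 + ((0.50² + 1) × 75 − 1) × 0.01 = 1.927

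The effective n is 750/1.927 = 389 per arm. Power for 60% against 70%, two-sided 5%, is 83.4%, close to the stated 85%.

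**Illustration A: a mixture tied to the 60% planning rate.** All step rates are assumed. In the facility arm 70% of declared children start and 86% of those complete: 0.70 × 0.86 = 60.2% of declared. In the community arm 90% start, and completion is truly 5 points better in every child. Let c be the completion that the extra 20% of children would have under facility care.

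- Community completion among declared = 0.70 × 0.91 + 0.20 × (c + 0.05)
- Non-completion among starters = 1 − (that figure)/0.90

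| c | Declared, facility → community | Non-completion among starters, facility → community |
|---|---|---|
| 40% | 60.2% → 72.7% | 14.0% → 19.2% |
| 50% | 60.2% → 74.7% | 14.0% → 17.0% |
| 63.5% | 60.2% → 77.4% | 14.0% → 14.0% |
| 86% | 60.2% → 81.9% | 14.0% → 9.0% |

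The sign reverses only for c below 63.5%. Above that the benefit shows but is diluted. At c = 86% there is no bias.

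**Illustration B: one latent family propensity.** Starting and completing are both logistic in a standard normal propensity with the same slope. Assumed inputs: 65% start in the facility arm, 90% in the community arm, and 78% would complete if everyone started. The figures come from numerical integration.

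| Slope per SD | Facility, completion among starters | Community, no true effect | Spurious difference | True gain at OR 1.25 if all started | Gain seen among starters |
|---|---|---|---|---|---|
| 0.5 | 79.4% | 78.4% | −1.0 | +3.5 | +2.4 |
| 1.0 | 82.5% | 79.5% | −3.0 | +3.1 | 0.0 |
| 1.5 | 85.9% | 80.9% | −5.0 | +2.7 | −2.4 |

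With the true OR of 1.25, completion among declared children rises at every slope: 51.6% to 73.7%, 53.7% to 74.3% and 55.9% to 75.1%.

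**Size against sampling error.** Starters per arm are 750 × 0.65 = 487.5 and 750 × 0.90 = 675. The design effects are 1 + (1.25 × 48.75 − 1) × 0.01 = 1.599 and 1 + (1.25 × 67.5 − 1) × 0.01 = 1.834. The standard error is the square root of the sum of p(1 − p) × DE/n over the two arms, which gives about 2.8 to 3.2 points. The spurious differences are therefore about 0.3, 1.0 and 1.8 standard errors, and the reversed −2.4 is about 0.9.

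**Started among eligible (assumed rates).** Facility: 75% of declared are found eligible and 93.3% of those start, so 70.0% of declared. Community: 97% are eligible, the same 75% start at 95.3% (a true +2 points), and the extra 22% start at 80%. The conditional rate is (0.75 × 0.953 + 0.22 × 0.80)/0.97 = 0.891/0.97 = 91.8%, a fall from 93.3%. Among declared children it rises from 70.0% to 89.1%.

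**The case against.** The primary endpoint already counts initiation with completion over all declared children and keeps losses, so a model that improves both is credited there. Step-to-step proportions are what a care cascade normally reports, and the Table 1 heading ties them to reasons for dropout. Both points stand. They support keeping the rows as description, not testing them as arm effects.

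Selection also acts in the community arm, because the index case must be willing to be visited and a second visit follows. This stands too: the direction is plausible, not fixed. The sizes rest on assumed inputs, and none of the spurious differences above would reach nominal significance on expectation.

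The sentence on dropout explains why lost children are kept in the primary analysis, and nothing says they are removed from the cascade rows. That is right, so there is no contradiction. What carries over is the reasoning that reaching a step can be a result of the model of care.

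The Statistical analysis section also compares register-based proportions between arms, and Table 1 lists register counts of children started. Neither uses declared children as its denominator, so neither supplies the missing initiation estimate.

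Finally, declared children are themselves counted after allocation in an unblinded trial. Their denominator is better protected, because it is fixed before the care routes diverge, but not perfectly so.

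**Conclusion.** The point holds for two secondary endpoints: starting among eligible children and non-completion among starters. Analysed as written, each gives an arm contrast open to selection bias. In the latent-propensity illustration a true gain of about 3 points is diluted under weak selection, hidden under moderate selection and reversed only at the strongest slope. In the mixture, reversal needs the extra children to complete below 63.5% against 86% in the others. These sizes rest on assumed starting rates, completion rates and strength of selection.

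A reader might infer that the trial's completion result is unreliable, or that a benefit will be reported as harm. The documents do not support that: the primary endpoint and the screened-among-declared endpoint are unaffected, and reversal is possible rather than expected. A reader might also infer that every cascade step is conditioned on the one before. Table 1 does not say so for the two eligibility rows. Nor is eligibility a matter of family behaviour alone, since it also depends on excluding TB disease and contraindications.

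**What to change.** Add one endpoint: started TPT among declared children (under 5 years, or HIV-infected and 5–14 years). Use it as the initiation endpoint in the between-arm mixed model. For the effect on completion, rely on the primary endpoint. Report the two step-conditional proportions by arm as descriptive, with reasons for dropout, or state that any arm contrast on them is not a causal effect.

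The cost is one added endpoint and a short change to the analysis text, with no new data. There are two downsides. Started among declared also counts children rightly not started because of TB disease or a contraindication, so those reasons should be shown by arm beside it. The conditional rates also lose their status as formal tests.
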